### Primary and secondary outcomes

The primary outcome of interest is the number of VFDs, defined as days alive and free from MV at day 28 from the onset of MV and from the day of randomization. For subjects ventilated for 28 days or more and for subjects who die, VFDs is 0. The secondary outcomes of interest include: length of invasive MV, length of post-extubation noninvasive ventilation, total assisted VFDs (invasive plus noninvasive), length of ICU and hospital stay, and ICU and hospital mortality, development of extrapulmonary organ failure (any organ failure developed during the study that was not present at the time of enrollment into the study) [22], prevalence of barotrauma (defined as the presence of any extrapulmonary air that was not present at study enrollment), ventilator-associated pneumonia (development of a pneumonia 48 h after study entry), development of ARDS after enrollment into the study, as defined by the American-European Consensus Conference (AECC) criteria for ARDS [23] or as moderate/severe ARDS by the Berlin criteria [17], and time from first SBT to extubation.

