## Abstract

**Background:**

Patient-ventilator asynchrony is a common problem in mechanically ventilated patients with acute respiratory failure. It is assumed that asynchronies worsen lung function and prolong the duration of mechanical ventilation (MV). Neurally Adjusted Ventilatory Assist (NAVA) is a novel approach to MV based on neural respiratory center output that is able to trigger, cycle, and regulate the ventilatory cycle. We hypothesized that the use of NAVA compared to conventional lung-protective MV will result in a reduction of the duration of MV. It is further hypothesized that NAVA compared to conventional lung-protective MV will result in a decrease in the length of ICU and hospital stay, and mortality.

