**Methods/design:**

This is a prospective, multicenter, randomized controlled trial in 306 mechanically ventilated patients with acute respiratory failure from several etiologies. Only patients ventilated for less than 5 days, and who are expected to require prolonged MV for an additional 72 h or more and are able to breathe spontaneously, will be considered for enrollment. Eligible patients will be randomly allocated to two ventilatory arms: (1) conventional lung-protective MV (*n* = 153) and conventional lung-protective MV with NAVA (*n* = 153). Primary outcome is the number of ventilator-free days, defined as days alive and free from MV at day 28 after endotracheal intubation. Secondary outcomes are total length of MV, and ICU and hospital mortality.

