### Data analysis

Data will be collected in each participating ICU using a standardized form. Data will be transmitted to the coordinating center whenever a patient dies or is discharged from the hospital. Before exporting the data into a computerized data base at the coordinating center, a trained data collector from the coordinating center will check the completeness and the quality of information. Logical checks will be performed for missing data and to find inconsistencies, especially regarding clinical diagnosis, date, and ventilatory parameters. If necessary, the data collector will contact the investigator by phone to validate the data or reformat the data for entry into the database.

Descriptive statistics will be expressed as mean ± SD or median and interquartile range depending on the nature and distribution of the variables. Inferential statistics will use estimates of the mean of the differences and their 95 % confidence intervals (CI). Variables normally distributed will be compared with the Student’s *t* test. For variables without a normal distribution, the Mann-Whitney *U* rank test will be used for comparison. Categorical variables will be compared using Fisher’s exact test. The primary outcome variable (number of VFDs) will be assessed with the Student’s *t* test or the Mann-Whitney *U* rank test dependent on the distribution of the data. The relative risks and their 95 % CIs will be estimated. For all these comparisons, we will consider a difference to be statistically significant if *p* < 0.05.

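### Length of MV and of ICU and hospital stay are to be compared by t or Mann-Whitney test with no rule for death, so a duration ended by death counts as a short one

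*Protocol article*

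**What the plan says.** The section on primary and secondary outcomes gives one rule for death, and it concerns the primary outcome: "For subjects ventilated for 28 days or more and for subjects who die, VFDs is 0". The same section lists as secondary outcomes "length of invasive MV, length of post-extubation noninvasive ventilation", then, among others, ICU and hospital length of stay and, last, "time from first SBT to extubation". None of the durations has a rule for patients who die. The abstract puts length of MV first among its secondary outcomes: "Secondary outcomes are total length of MV, and ICU and hospital mortality".

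The Data analysis section chooses the test by the shape of the distribution: "Variables normally distributed will be compared with the Student’s *t* test", and "For variables without a normal distribution, the Mann-Whitney" test is used otherwise. All these comparisons are judged at p < 0.05. The sample size section says that enrolled and randomized patients are analysed. The Data analysis section says that data are sent when a patient dies or leaves hospital. No survivors-only set, worst-rank value or competing-event method is stated for any duration.

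The abstract's background states the hypothesis that NAVA "will result in a reduction of the duration of MV", followed by shorter ICU and hospital stay and lower mortality. The justification section repeats the first two.

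**The concern.** Death ends both ventilation and stay. A patient who dies on the ventilator on day 3 has a 3-day length of MV, and a t or rank test cannot tell that from a patient liberated on day 3. If the arms have equal mortality and a similar timing of deaths, this adds noise but does not favour either arm. If mortality differs, the test responds to the deaths as well as to the speed of liberation. Equal mortality cannot be assumed here, because lower mortality is one of the trial's own hypotheses.

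The result could mislead in either direction. An arm with more early deaths could be reported as having significantly shorter MV or stay, or a real gain in speed of liberation could be hidden because that arm kept more patients alive.

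Time from first SBT to extubation raises a related problem. It exists only for patients who reach both events, so the comparison by arm is among patients selected after randomization. The same holds for length of post-extubation noninvasive ventilation if it is restricted to extubated patients.

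**Working it through.** **The plan's own figures.** The article gives no figure for length of MV or stay, so there is none to reproduce. The only number borrowed is 153 per arm. It comes from the VFD calculation and is not in question here.

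**Assumptions (not from the article).** MV length is log-normal, with median 8 days and log-SD σ = 0.7 in survivors of both arms. In patients who die it is multiplied by m. Mortality is 20% in one arm and 30% in the other. The test is Mann-Whitney, two-sided at 0.05. Survivors have identical MV times in both arms, so any excess over 2.5% in one direction comes from the deaths alone.

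**Formula.** Let θ be the probability that a random patient of the higher-mortality arm has a shorter duration than a random patient of the other arm. Let Φ* = Φ(−ln m / (σ√2)). Pairs with the same vital status contribute one half. The other pairs contribute Φ* or 1 − Φ*:

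θ = (0.30 × 0.80)Φ* + (0.70 × 0.20)(1 − Φ*) + ½(0.06 + 0.56) = 0.45 + 0.10Φ*

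The median of 8 days cancels out. The null standard error is √((2n+1)/(12n²)) = √(307/280,908) = 0.0331. With z = (θ − 0.5)/0.0331, the chance of a significant result in favour of the higher-mortality arm is about Φ(z − 1.96).

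| m | Φ* | θ | z | Approximation | Simulation |
|---|---|---|---|---|---|
| 0.4 | 0.82 | 0.532 | 0.98 | 16.3% | about 16% |
| 0.6 | 0.70 | 0.520 | 0.60 | 8.6% | about 8% |
| 0.8 | 0.59 | 0.509 | 0.27 | 4.5% | about 4% |
| 1.0 | 0.50 | 0.500 | 0.00 | 2.5% | about 3% |
| 1.3 | 0.40 | 0.490 | −0.32 | 1.1% | about 1% |

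The two columns agree within simulation error. At m = 1.3 the bias runs the other way: about 4% of simulated trials are significant against the higher-mortality arm.

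**Other mortality gaps, m = 0.6 and 0.4.** Simulation gave 5% to 8% at 20% v 25%, and 14% and 32% at 20% v 35%. With equal mortality it gave 2.4% and 2.6%.

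**A different model.** Here the time to liberation is the same in both arms (log-normal, median 8 days, log-SD 0.8), and death on MV occurs at a constant hazard. At 20% v 30% mortality, mean length of MV is 9.0 v 8.0 days. The higher-mortality arm is significantly shorter in about 20% of trials by either test. Restricting to survivors does not cure this: 9.3 v 8.5 days, with 10% significant in the same direction. This model cuts courses short by death, so its direction is built in.

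**The primary outcome under the same models.** With death scored 0, mean VFDs in the constant-hazard model are 15.2 v 13.8, so the arm with more deaths looks worse, as it should. In the multiplier model, VFDs significantly favoured the higher-mortality arm in at most 0.1% of runs at gaps of 10 to 15 points.

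**The case against.** Four arguments weigh against the point.

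- **The primary outcome already guards against this.** A reader might infer that excess mortality could make the trial's main hypothesis appear confirmed. The article does not support that. The trial is powered on VFDs, its Background section words the hypothesis as a gain in VFDs, death scores 0, and ICU and hospital mortality are outcomes in their own right. This argument stands, and it confines the point to secondary claims.
- **The article never says that death counts as a success.** That is true. The test paragraph is general and does not name length of MV or stay, and an analysis plan that is not shown may say how deaths enter. But the article does more than stay silent: it fixes the test for continuous variables and confines its death rule to VFDs. A later plan would have to replace that choice, not merely add detail.
- **Size and direction are assumed.** This also stands. A reader might infer that the arm with more deaths always gains, but the bias vanishes at m = 1.0 and reverses above it. The article gives no mortality rate. Its exclusions (moderate or severe ARDS, three or more organ failures, poor short-term prognosis) give no ground for expecting a large gap.
- **NIV length could be recorded as 0 in patients who receive none.** If so, it is defined for everyone and the selection problem falls away. Hence the condition attached to it above.

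**Conclusion.** The point holds for the secondary outcomes length of invasive MV and length of ICU and hospital stay. As written, the stated tests treat a duration ended by death as a short one, so a difference in mortality is carried into the comparison. The consequence is a possibly misleading secondary statement about hypotheses that the article itself puts forward, not a false primary result.

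At 153 per arm and 20% v 30% mortality, the chance of a spurious significant result for the arm with more deaths runs from about 16% (m = 0.4) through the nominal level (m = 1.0) to about 1% (m = 1.3), where the bias is reversed. The constant-hazard model gives about 20%. These figures depend on assumed mortality and on how early deaths occur. What does not depend on them is that the stated comparison does not separate death from liberation or discharge. This should be corrected, but the trial's main conclusion does not rest on it.

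**What to change.** Replace the t or Mann-Whitney comparison of these durations with time from randomization to liberation from invasive MV, to ICU discharge alive and to hospital discharge alive, each with death as a competing event. Show cumulative incidence by arm, with a subdistribution or a cause-specific hazard ratio chosen in advance. Report raw lengths of MV and stay separately for survivors and non-survivors, as description without a test. Label time from first SBT to extubation as descriptive, and do the same for NIV length if it is restricted to extubated patients.

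The cost is some added analysis in standard software and a definition of liberation that handles reintubation, which the article does not give. The article already provides for data on the last day of invasive support, vital status to ICU discharge, and hospital stay and mortality. The event times should follow from these, but the case report form should be checked to confirm that the dates are there. The sample size, which rests on VFDs, does not change.

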## Methods/design

### Justification of the study

Patient-ventilator asynchrony is a common problem in mechanically ventilated patients with ARF who are receiving assisted ventilation. Based on new data, all patients managed with conventional modes of MV have an AI > 5 % at various points during the day [3]. NAVA is a unique approach to MV based on neural respiratory output, providing a smooth transition to natural breathing. NAVA better assures that the patient’s breathing is in synchrony with, and in proportion to, the patient’s own efforts, regardless of patient category or size.

We justify the need for our study based on the fact that NAVA can provide a smooth transition to natural breathing. We hypothesized that the use of NAVA compared to conventional lung-protective MV will result in a decrease in the number of days of MV. It is further hypothesized that NAVA will result in a decrease in the length of ICU and hospital stay. The goal of this study is to compare the ability of NAVA versus conventional lung-protective MV to provide invasive ventilatory support during ARF in adults who are expected to require ventilatory support for at least 72 h.

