When an appropriate fluid challenge fails to restore adequate blood pressure and organ perfusion, therapy with vasopressor agents should be started. Either norepinephrine or dopamine (through a central catheter as soon as available) is the first-choice vasopressor agent to correct hypotension in septic shock. Vasopressin may be considered in patients with refractory shock despite adequate fluid resuscitation and high-dose conventional vasopressors. These recommendations may be revised as the new surviving sepsis guidelines become available. In patients with low cardiac output despite adequate fluid resuscitation, dobutamine may be used to increase cardiac output. If used in the presence of low blood pressure it should be combined with vasopressor therapy. A strategy of increasing Cardiac Index to achieve an arbitrarily predefined elevated level is not recommended.

Enteral nutrition should be provided as soon as it is deemed safe by the treating physicians. Exogenous insulin should be provided with the goal of achieving a blood glucose level below 150 mg/dl for the first 3 days of critical illness. If, after 3 days, enteral nutrition has been established and other resuscitation measures have been provided, a goal of normoglycemia (110–140 mg/dl) should be considered. This approach should minimize the potential impact of hypoglycemia. Ongoing randomized controlled trials may change these recommendations, in which case we will provide protocol amendments if necessary.

Data on lung mechanics, gas exchange, and hemodynamics will be gathered before applying study settings, then after applying study settings at times 0, 4 h, 24 h, 48 h, 96 h, 7 days, 10 days, 14 days, and every 7 days thereafter and on the last day of invasive ventilatory support (Table 1). At initiation of the protocol and at 4 h, data collected will represent one point in time, that is individual data will be coupled. However, each day after that data will not be coupled since the highest and lowest value for each variable will be recorded. It is expected that this data will be collected between 8 a.m. and 12 noon each day. Also, at this time the maximum Edi (the peak inspiratory value) will be reassessed and readjustments of MV will be made if necessary. Patients will be followed-up (alive or dead) until ICU discharge. In addition, we will record hospital length of stay and mortality.

**Table 1 Tab1:** Schedule of events

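### ICU and hospital mortality, the only mortality outcomes named, are counted over a stay that NAVA is expected to shorten, so part of an apparent mortality difference could reflect earlier discharge

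*Protocol article*

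**What the plan says.** The outcomes section (Primary and secondary outcomes) lists "length of ICU and hospital stay, and ICU and hospital mortality". The abstract names the same two: "Secondary outcomes are total length of MV, and ICU and hospital mortality". No section shown names mortality at a fixed day.

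The abstract's Background hypothesizes that NAVA "will result in a decrease in the length of ICU and hospital stay, and mortality". Justification of the study repeats the part on stay: "It is further hypothesized that NAVA will result in a decrease in the length of ICU and hospital stay".

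On follow-up, the section on general care states "Patients will be followed-up (alive or dead) until ICU discharge", and then "In addition, we will record hospital length of stay and mortality". Under Data analysis, forms go to the coordinating center at death or hospital discharge. The text shown plans no check of vital status after that.

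On analysis, the same section says "Categorical variables will be compared using" Fisher's exact test, adds relative risks with 95% confidence intervals, and sets significance at p < 0.05.

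**The concern.** ICU and hospital discharge happen after randomization, and the trial expects the intervention to bring both forward. If it does, NAVA patients spend fewer days in which a death can be counted. A death on a given day can then be an ICU death in the control arm, while the same death in a NAVA patient who left the ICU the day before is recorded as ICU survival. Fisher's test and a crude relative risk make no allowance for this.

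The distortion runs in the direction the trial hopes for. Treatment is not blinded, and the staff who know the allocation also manage and follow the patients. An absence of benefit, or a small harm, could also be partly hidden. At stake is whether the mortality hypothesis in the abstract can be answered cleanly.

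**Working it through.** **The plan's own figures.** The article gives no mortality rate, length of stay or power for mortality, so there is no mortality figure to reproduce. Two planning figures are used below: 21 VFDs with SD 6, and 153 patients per arm. The point does not depend on how 153 was derived.

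**Step 1: ICU mortality when treatment has no effect on death.** Assume a constant death hazard h per day, the same in both arms and both in and out of ICU, and an exponential time to ICU discharge with mean L days in the absence of death. Then

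P(ICU death) = h / (h + 1/L).

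The stays of 12 v 10 days are assumed. Day-28 mortality is 1 − exp(−28h), identical in both arms.

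| h per day | ICU mortality, L = 12 | L = 10 | Difference (points) | RR | Day-28 mortality, both arms |
|---|---|---|---|---|---|
| 0.0028 | 3.3% | 2.7% | 0.5 | 0.84 | 7.5% |
| 0.01 | 10.7% | 9.1% | 1.6 | 0.85 | 24% |
| 0.02 | 19.4% | 16.7% | 2.7 | 0.86 | 43% |
| 0.03 | 26.5% | 23.1% | 3.4 | 0.87 | 57% |

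At h = 0.02 with 12 v 11 days, the RR is 0.93.

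**Step 2: which death rate fits the planning figures.** Deaths score 0 VFDs. If a fraction p of patients scores 0 and the overall mean is 21, the rest average 21/(1 − p). The variance is then at least p(1 − p) × [21/(1 − p)]² = 441p/(1 − p). With SD 6 this cannot exceed 36, so p/(1 − p) ≤ 36/441 and p ≤ 36/477 = 7.5%. The matching hazard is −ln(1 − 0.0755)/28 = 0.0028 per day, the first row of the table. In 153 patients the difference is 153 × 0.0053 = 0.8 of a death.

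The higher rows do not fit these figures. At 43% dead, mean VFDs cannot exceed 28 × 0.57 = 16.

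**Step 3: a lower hazard after ICU discharge.** Let the ICU hazard be h = 0.02, the post-ICU hazard g = 0.004 (one fifth), m = 1/L and k = h + m. Then

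day-28 mortality = 1 − {exp(−28k) + [m/(k − g)] × [exp(−28g) − exp(−28k)]}.

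L = 12 gives 24.1% and L = 10 gives 22.4%, so the day-28 RR is 0.93 against an ICU RR of 0.86. The real part is (1 − 0.93)/(1 − 0.86), about half. At one tenth of the hazard the day-28 RR is 0.91.

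**Step 4: hospital mortality.** A simulation gave both arms the same death times (30% dead by day 90), made discharge independent of prognosis, and cut the ICU stay by 2 days. All of these are assumptions.

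| Outcome | Control | NAVA | RR |
|---|---|---|---|
| ICU mortality | 13.6% | 11.9% | 0.88 |
| Hospital mortality | 20.3% | 19.3% | 0.95 |
| Day-28 mortality | 22.6% | 22.6% | 1.00 |

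**Step 5: chance of a false significant result.** With 153 per arm and Fisher's test at 0.05, a pure artefact of 19.4% v 16.7% gives a significant result favouring NAVA in about 6.5% of simulated trials (6.7% by exact enumeration). With no difference the figure is 1.8%. For the hospital figures in step 4 it is 3.0%.

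**The case against.** The strongest reply is that the effect is small and partly genuine. Patients are usually discharged because they have recovered, and the trial expects shorter stays through earlier liberation from the ventilator. If risk falls after ICU, some of the lower ICU mortality is a true benefit (step 3). At the death rate the planning figures allow, the artefact is under one death per arm (step 2). Both replies stand and limit the size. Neither makes the counting windows equal. The planning figures may also be optimistic, and at higher death rates the absolute gap grows.

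Mortality is also secondary here. The Methods hypothesis names stay but not mortality, the Background section speaks only of a potential survival gain, and death already enters the primary outcome through VFDs. This holds too, but VFDs mix death with ventilation time and give no estimate of mortality, and the abstract does make lower mortality a hypothesis.

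The outcome list is open-ended, and an article condenses a fuller protocol. Yet the article itself states the outcomes, the end of follow-up and the test, and points to no other mortality outcome.

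A reader might infer that both outcomes are biased by some 15%, or that a false mortality claim is likely. The documents support neither. They give no rates, hospital mortality still captures ward deaths, and step 5 shows that a false significant result is uncommon.

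**Conclusion.** The point holds as a limited flaw in the choice of outcome. The windows for ICU and hospital mortality depend on discharge, which NAVA is expected to hasten, and the planned comparison does not allow for that. ICU mortality is mainly affected, and hospital mortality less.

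The documents do not fix the size. With equal hazards in and out of ICU and mean stays of 12 v 10 days, the ICU RR is about 0.84 to 0.87 with no effect on death. The absolute gap is about 0.5 points at the death rate implied by 21 VFDs (SD 6). About half of the relative effect is real if the post-ICU hazard is one fifth of the ICU hazard. If NAVA does not shorten stay, this bias does not arise. The consequence is a relative risk that is hard to interpret, more than a likely false claim. It is worth correcting because the correction is cheap.

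**What to change.** In Primary and secondary outcomes, add all-cause mortality at day 28 from randomization for every randomized patient, wherever they are on that day. Use it to test the mortality hypothesis, and report ICU and hospital mortality as supportive. In the follow-up text, state that vital status is obtained to day 28 after discharge as well.

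The cost is outcome wording and a record check or call for patients who leave hospital before day 28. The primary outcome already needs vital status to day 28, so little of this is extra work. Sample size and trial treatment do not change.
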